### Secondary outcome measures

To assess the difference in recovery from depression between the I-Sleep and usual care groups over a period of 12 months after baseline, logistic mixed models will be used to account for repeated measurements within patients. To assess the difference in the improvements in insomnia symptom severity, daily functioning, and quality of life over time between the I-Sleep and usual care groups, linear mixed models will be used to account for repeated measurements within patients. Three hierarchical levels will be included in the logistic and linear mixed models: mental healthcare outpatient clinic for mood disorders, patient and time. The primary effect is described by the coefficient of the time-treatment interaction term. If necessary, the analysis will be adjusted for confounders and/or stratified for effect modifiers.

### Economic evaluation

In the economic evaluation, we will relate the incremental costs of I-Sleep in addition to usual care for depression in comparison with usual care alone to the incremental health effects. We will perform both a cost-effectiveness analysis (CEA) and a cost-utility analysis (CUA) from a societal and healthcare perspective according to Dutch guidelines [39]. The time horizon of the economic evaluation is 12 months, making discounting unnecessary. The following effect measures will be included in the economic evaluation: 1) Severity of depressive symptoms (PHQ-9); 2) Recovery from depression (PHQ-9); 3) Sleep quality (ISI); 4) Quality-Adjusted Life-Years.

Multiple imputation according to the MICE algorithm will be done to impute missing cost and effect data [40]. To estimate cost and effect differences between intervention and control while adjusting for confounders if necessary linear regression analyses will be used in every imputed dataset. Next, Rubin’s rules will be used to pool the results from the different datasets. We will calculate Incremental cost-effectiveness ratios (ICERs) by dividing the difference in the mean total costs between the treatment groups by the difference in mean effects between the treatment groups. To estimate statistical uncertainty around the cost differences and the ICERs bias-corrected and accelerated bootstrapping with 5000 replications will be used. To graphically present uncertainty surrounding the ICERs cost-effectiveness planes will be used. The probability that the intervention is cost-effective in comparison with control for a range of different ceiling ratios, i.e., the decision uncertainty, will be shown using cost-effectiveness acceptability curves [41].

### Data management and quality assurance

The data of each participant will be stored in a case record form (CRF patient data file) on each study site. The CRF is available only to the research team on site and will not be disclosed to a third party. Participants in the EINSTEIN study will be pseudonymised, i.e., each participant will be identified by a four-digit number that contains no identifiable information. The master key connecting names to the code will be safeguarded by the principal investigators on each study site only. All data is collected digitally and de-identified using a four-digit code number via Castor, a certified online electronic data capture system for medical research. Except for the qualitative interviews with patients, therapists, and managers from each mental healthcare outpatient clinic for mood disorders during and at the end of the study period held for process evaluation purposes. Audio records of the interviews will be securely stored at the digital storage facilities of each participating location only for as long as it takes to transcribe the interview anonymously since we intend to publish the pseudonymised transcripts (instead of the audiotapes). Additionally, an administrative database will be used on each study site to ensure timely assessments and log any other relevant research activities. At the end of the trial, once collected, the anonymised interview transcripts, the de-identified baseline data, log files of the internet program, the de-identified database data, log files of research activities, and the follow-up data collected from all mental healthcare outpatient clinics will be stored safely at the Department of Research and Innovation of GGZ inGeest. All data will be processed, backed up periodically, and managed by the data management team of GGZ inGeest. Data will be handled confidentially complying with the General Data Protection Regulation (GDPR) and in accordance with the Dutch Medical Research Involving Human Subjects Act (WMO). Likewise, both Castor and the Minddistrict platform on which the I-Sleep intervention runs, comply with all the applicable laws and regulations, including ICH E6 Good Clinical Practice (GCP), 21 CFR Part 11, EU Annex 11, General Data Protection Regulation (GDPR), HIPAA (US), ISO 9001 and ISO 27001. Following a risk assessment of the EINSTEIN study, installing a data and safety monitoring board was deemed unnecessary considering it is not expected that the I-Sleep intervention in this study will cause additional harm or risk to participants. Documentation on the research project will be archived. Research data of the study will be stored and kept for fifteen years upon completion of the EINSTEIN trial and after the publication of the results, after which they will be destroyed.

### Adverse event reporting

All adverse events (AEs) reported spontaneously by the subject or observed by the investigator or staff will be recorded. Serious adverse events (SAEs) for this study are unforeseen. However, SAEs that might be related to the investigational CBTi treatment defined as suicide or acute aggravation of psychiatric symptoms which necessitates additional intervention, such as manic or psychotic episodes will be reported to the sponsor without undue delay. The sponsor will report the SAEs to the accredited METC according to its requirements. SAEs will be followed until they have abated, or until a stable situation has been reached. Given the nature of the investigational treatment, no other serious adverse events directly related to the I-Sleep program are expected.

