## Background

Major depression is one of the most common mental disorders worldwide, with currently over 264 million people suffering from depression globally [1]. With a lifetime prevalence of 18.7% and a 12-month prevalence of 5.2% in the Netherlands, it is estimated that each year 546,500 people suffer from depression in the Netherlands [2]. Depression is associated with severe functional impairments, and high societal expenditures due to increased healthcare utilization and productivity losses [3–5]. In Europe, the total costs of major depression were estimated to be €92 billion in 2010, of which €38 billion concerning healthcare and patient costs, and €54 billion concern lost productivity costs [6].

Insomnia has a high prevalence as well with estimates for chronic insomnia ranging from 10 to 15% and for transient or occasional insomnia from 25 to 35% in the general adult population [7]. The societal consequences of insomnia are significant and include costs of insomnia treatments, increased health care utilization, decreased workplace productivity, and an increased accident risk [8].

Depression and insomnia often co-occur. It is estimated that of people with insomnia, 40% suffer from depression and that 80% of patients with depression also suffer from insomnia [9]. Moreover, patients with depression and insomnia have lower quality of life [10]. and worse treatment outcomes compared to patients with depression alone [11]. Furthermore, suicidal ideation is more common in this group than among patients with depression alone [11, 12]. Finally, patients who still experience insomnia after successful depression treatment are at higher risk of recurrent depression [13, 14].

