### Randomization, blinding and treatment allocation

After inclusion, participants are randomly assigned to either the intervention group I-Sleep (before the start of the usual care) or the control group (usual care alone) on a 1:1 ratio. Variable block sizes are used. Randomization takes place at the patient level and is stratified by mental health outpatient clinics for mood disorders. An independent researcher has created an allocation scheme using a computerized random number generator (Castor). Randomization will be performed by another independent research assistant who reveals the randomization outcome. Due to the nature of the intervention, blinding of patients, therapists, researchers and research assistants was not possible.

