Likewise, due to a study protocol with randomisation and control group, we may experience a limitation in the number of patients that would want to participate. Patients or “potential participants” find it difficult to understand that only 50% of the participants will be treated with I-Sleep and that this will be determined by randomization. At the same time, some patients insist on starting treatment with the regular depression care immediately and this is not possible when randomised to the I-Sleep condition. The randomisation procedure therefore possibly complicates the recruitment of potential participants.

In summary, adding guided online CBTi to usual care for depression in outpatient clinics for mood disorders might be an effective and cost-effective alternative to usual care alone. This study will evaluate the (cost) effectiveness of I-Sleep for depression while simultaneously assessing the feasibility of implementation of I-Sleep in primary and secondary mental healthcare.

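### SAE reporting to the sponsor is conditioned on possible relatedness to CBTi, so the SAEs reported this way are not comparable between the arms

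*Protocol article*

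**What the plan says.** The section "Adverse event reporting" of the protocol article works in two layers.

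- **Recording.** "All adverse events (AEs) reported spontaneously by the subject or observed by the investigator or staff will be recorded". This sentence sets no limit by arm, seriousness or relatedness.
- **Reporting.** The SAEs to be passed promptly to the sponsor are "SAEs that might be related to the investigational CBTi treatment defined as suicide or acute aggravation of psychiatric symptoms which necessitates additional intervention", with manic and psychotic episodes as examples. Then: "The sponsor will report the SAEs to the accredited METC according to its requirements". The section closes by saying that "no other serious adverse events directly related to the I-Sleep program are expected".

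Other sections bear on how the reporting rule works:

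- Randomization, blinding and treatment allocation: "blinding of patients, therapists, researchers and research assistants was not possible". I-Sleep comes before usual care starts, and allocation is 1:1.
- Usual care: therapists are asked not to give CBTi.
- Discussion: "some patients insist on starting treatment with the regular depression care immediately and this is not possible when randomised to the I-Sleep condition".
- Data management and quality assurance: no data and safety monitoring board, because I-Sleep is not expected to add harm or risk.
- Background: "suicidal ideation is more common in this group than among patients with depression alone", the group being patients with both depression and insomnia.

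**The concern.** The reporting rule is stated outright, so this is not a detail that a condensed article has left out. It makes reporting depend on a possible causal link to a treatment that only one arm is meant to receive. The filter therefore works differently in the two arms, and the person applying it knows the allocation.

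The arms also differ in when regular depression care begins. A patient might deteriorate while that care has yet to start. Staff could put this down to the depression or to the sequencing of treatment and not to CBTi, and so leave it unreported. Serious psychiatric events are plausible in both arms of this population. With no monitoring board, the sponsor and the ethics committee are the only oversight bodies that the article describes, and both see SAEs only after the filter.

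**Working it through.** The article gives no SAE rate, safety sample size or safety power, so there is no figure to reproduce. The check is how the rule behaves in each arm.

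**Inputs**

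- n per arm: 175 / 2 = 87.5, so 87 or 88 (Sample size; 1:1 allocation).
- p_I and p_C: true SAE risk in the I-Sleep and usual-care arms. Not given, so left as symbols.
- r_I and r_C: share of SAEs in each arm that staff judge possibly related to CBTi. Not given, so left as symbols.

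**Step 1: what reaches the sponsor.** The expected number reported is n × p_I × r_I for I-Sleep and n × p_C × r_C for usual care. The ratio of reported to reported is (p_I / p_C) × (r_I / r_C). The quantity of interest is p_I / p_C, so the reported ratio is correct only if r_I = r_C.

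**Step 2: the usual-care arm.** These patients are not meant to receive CBTi, so on the literal reading r_C = 0. The reported count is n × p_C × 0 = 0 for every value of p_C.

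**Step 3: false excess.** Let the true risks be equal, p_I = p_C = p. The reported difference is n × p × r_I − 0, which is positive whenever p and r_I are above zero. Oversight sees I-Sleep events only, though the risks are the same.

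**Step 4: missed excess.** Suppose p_I is larger than p_C, but staff attribute most I-Sleep events to the depression or to the later start of depression care. Then r_I is near 0 and n × p_I × r_I is near 0, however large the true excess.

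**Step 5: reporting without the filter.** With r_I = r_C = 1 the reported ratio is p_I / p_C. Dropping the relatedness condition removes the distortion, and no assumption about the SAE rate is needed to show this.

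**Step 6: can the scheduled questionnaires stand in?** Table 1 has the PHQ-9 at T1 to T4 in both arms, which is symmetric and useful. The PHQ-9 covers the previous two weeks (Primary outcome). T1 is 3 months after T0, about 52 / 4 = 13 weeks, so the first follow-up score describes roughly weeks 11 to 13. I-Sleep lasts five weeks. If it starts close to baseline (an assumption, as the article gives no interval), it ends around week 5, some 11 − 5 = 6 weeks before that window opens. An acute episode during I-Sleep that had settled by then would not show. The questionnaires therefore supplement SAE reporting and do not replace it.

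**The case against.** The strongest reply is that recording and reporting are different things. Reported or observed adverse events are recorded without regard to arm, which on a plain reading includes serious events under usual care. A trial report can be built from those records. This stands. A reader might infer that harms cannot be compared between arms at all, or that adverse events rest on patients' own reports alone. The article supports neither: staff observation is included, and the PHQ-9, ISI, WSAS, EQ-5D-5L and iMCQ follow one schedule in both arms.

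The rule can also be read more generously. Possible relatedness is a low threshold, and the definition may be meant as a list of event types to report in either arm. The text does not say so, and that ambiguity is itself worth removing. The Discussion presents I-Sleep as the start of depression treatment, so some staff would count the sequencing as part of the investigational treatment; others might not.

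Two further inferences are tempting and fail:

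- That extra I-Sleep contacts inflate adverse event counts in that arm. Usual care brings therapist contact too, and the net difference is not stated, so neither the direction nor the size of such a bias is shown.
- That "Serious adverse events (SAEs) for this study are unforeseen" contradicts the events then named, or the Background. The wording that follows is ordinary contingency wording, and raised suicidal ideation in a population is not the same as harm expected from I-Sleep.

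Finally, this is a condensed article. The full SAE definition, the reporting window and the way adverse events are elicited may stand in the full protocol, and their absence here is no finding. That does not reach the relatedness condition, which the article itself states.

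**Conclusion.** The point holds in a limited form. As written, SAE reporting to the sponsor and the ethics committee depends on possible relatedness to CBTi, judged unblinded, in a trial without a monitoring board. SAEs reported by this route are not comparable between arms, and the distortion can go either way. For harms overall, the comparison is at risk of bias but not ruled out, because adverse events are recorded in both arms.

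No number of lost or excess reports can be given: the documents state no SAE rate, and any assumed rate would be unsupported. The conclusion rests on two readings of the text: that the condition is applied as worded, and that usual-care patients do not receive CBTi. If the full protocol already has all SAEs reported in both arms, only the article's wording is at fault. The primary outcome and its analysis are not affected.

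**What to change.** - Replace the relatedness condition with reporting of all SAEs in both arms, from randomisation to month 12.
- Record judged relatedness as a separate field that does not decide whether an event is reported.
- Tabulate SAEs by arm.
- Add a by-arm table from data already collected at T1 to T4: worsening on the PHQ-9 from baseline, the PHQ-9 suicidality item, and acute care or admissions where the iMCQ captures them.

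The cost is a few sentences in the safety section and a few more SAE reports from the four clinics. The supplementary table needs no new data collection.

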### Data dissemination

Data will first be analysed by the researchers involved in the project. After a stipulated embargo period the depersonalised data, statistical code, and study protocol will be made accessible for further research and verification upon reasonable request (including a data-analysis plan) and after permission from a (to be installed) steering committee. GGZ inGeest will process the collected data and will disclose both positive and negative findings unreservedly. Results from the EINSTEIN study will be submitted for publication to peer-revied scientific journals and disseminated through presentations at scientific conferences. Findings will be communicated with participants through the websites of participating outpatient clinics for mood disorders and the Dutch Depression Association.

## Discussion

This study is to our knowledge, the first to investigate the effectiveness and cost-effectiveness of adding I-Sleep to care as usual in a population receiving treatment for unipolar depression at several outpatient clinics for mood disorders within the Netherlands. Combining both quantitative and qualitative measures will result in a thorough overview of the effectiveness, cost-effectiveness, and feasibility of I-Sleep in depression treatment. This will allow us to not only provide evidence on the effectiveness, and cost-effectiveness of I-Sleep, but through the RE-AIM process evaluation to also reflect on helping and hindering factors during the implementation process in clinical practice.

Results from this study will be important for several stakeholders. First, if the addition of I-Sleep to usual care of patients with both depression and insomnia proves to be effective, this will improve the treatment of depression in general. Therapists may benefit from the easy-to-use online protocol for the treatment of patients with depression and insomnia, and patients may experience better treatment outcomes. Second, the involvement of mental healthcare providers and representatives of depressed patients ensures that this information will then also be incorporated in clinical treatment decisions for patients with both depression and insomnia. Third, if the cost-effectiveness of I-Sleep has been confirmed, this will be an incentive for mental healthcare institutions to make I-Sleep available for therapists in their organisations on a regular basis. Moreover, this is also expected to lead to reduced societal costs related to depression.

Additionally, an advantage of the I-Sleep intervention over regular CBTi is that it has a relatively low-threshold for patients to start with insomnia treatment, since they can work on treating their insomnia from the comfort of their own homes. Additionally, for therapists, the time investment needed to be trained in I-Sleep is small. I-Sleep builds on what is already known by experienced CBT therapists and less experienced therapists (e.g., general practitioners, nurse practitioners and experts by experience) can be trained in I-Sleep relatively quickly. With this small time-investment in training, I-Sleep also responds to the current work pressure and the general shortage of trained psychologists within the mental healthcare system.

Equally important, this RCT is based on a non-randomised pilot study within one outpatient mental healthcare clinic for mood disorders in which I-Sleep for depression proved to be effective. However, the findings also showed room for improvement in the applicability of I-Sleep in clinical practice. The ‘I-Sleep for depression protocol’ for this RCT was adapted based on the results of this pilot study to facilitate implementation in clinical practice and to reduce the drop-out rate of participants. The following adjustments were made. First, during the pilot study I-Sleep was offered simultaneously with usual care, but this was too much of a burden for the participants. I-Sleep is now offered as part of the depression treatment; the treatment starts with I-Sleep and, after completing the I-Sleep program, treatment continues according to the care-as-usual principle if necessary. We believe that this adjustment will procure a higher percentage of participants finishing the entire I-Sleep program. Secondly, during this RCT I-Sleep is preferably given by the same clinician as the subsequent usual depression treatment. Lastly, we have chosen to offer I-Sleep as a guided intervention instead of entirely as a self-help module. This may increase the acceptance and effectiveness of the treatment offered in people with depression [42].

Besides, many of the available studies on the effect of I-Sleep on insomnia have been conducted in the general population or in general practice patients with sleep problems. We are conducting research with I-Sleep in clinical practice among a population that is not yet well studied but experiences a huge suffering due to (clinically diagnosed) insomnia and depression. Which means that we will soon be able to present results that are relevant and generalizable to clinical practice, where the patients with these problems are found.

Needless to say, as in all studies, the scope of our design is limited. Within the current study design, we recruit patients from institutions that voluntarily applied for participation or with which good contacts already existed. This may cause a selection and/or convenience bias. It may be that these institutions are (more than others) already focused on treating patients with depression for insomnia-related symptoms as well. The contrast between the experimental condition and care as usual could therefore be smaller, which could lead to overly conservative estimates of the effect of I-Sleep.

Likewise, due to a study protocol with randomisation and control group, we may experience a limitation in the number of patients that would want to participate. Patients or “potential participants” find it difficult to understand that only 50% of the participants will be treated with I-Sleep and that this will be determined by randomization. At the same time, some patients insist on starting treatment with the regular depression care immediately and this is not possible when randomised to the I-Sleep condition. The randomisation procedure therefore possibly complicates the recruitment of potential participants.

In summary, adding guided online CBTi to usual care for depression in outpatient clinics for mood disorders might be an effective and cost-effective alternative to usual care alone. This study will evaluate the (cost) effectiveness of I-Sleep for depression while simultaneously assessing the feasibility of implementation of I-Sleep in primary and secondary mental healthcare.

